### Stratification and randomization

We extract data on prior cancer screening from EMRs using Common Procedural Terminology (CPT) codes, International Classification of Disease (ICD) codes, and home-grown codes from each health plan. Participants are stratified by screening status into three groups based on EMR data: up to date with screening based on USPSTF recommendations, screened in the past five years but not up to date with their screening, and eligible but not screened in the past five years. Participants are stratified by race and ethnicity with the goal of recruiting at least 25% Non-Hispanic Black participants and 25% Hispanic participants for the study population. If not enough available participants are available to recruit from a given stratum, we select additional participants from other strata. Random samples of eligible participants from each study site are sent to the UW Data Coordinating Center (UW DCC) for stratified randomization for initial survey modality (phone vs. web) and subsequent survey timing (1 vs 3 months) on a regular basis at KPWA, UW, and MHS. Due to administrative requirements at HFH, patients at this site ware randomly assigned to their survey modality but not their follow-up time. We select HFH patients for participation in two waves. Those selected in May 2023 were assigned to 3-month follow-up, whereas those selected in August 2023 were assigned to 1-month follow-up. To maximize study efficiency, we select people who are eligible for more than one screening exam based on EMR information. For example, we combine cervical and breast cancer screening questions for women ages 40–49 and breast, cervical, and colorectal cancer screening for women aged 50–65 (Table 2).

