### Sample size

A minimum of 500 gold-standard positive and negative participants for each cancer type are selected to obtain confidence interval width of <0.1 for sensitivities and specificities >0.80 across all survey modalities. A total study sample size of at least 1,576 individuals will contribute information to validity analyses of cancer screening history (Fig 1). For subgroups representing 20% (n = 100) of each cancer screening cohort, highly concordant screening tests (>0.9) and tests with good concordance (>0.8) will have 95% confidence interval widths of <0.12 and <0.16 respectively. We estimate that 1,260 (80%) participants would need to be included for the assessment of test-retest reliability across all screening modalities, resulting in >0.80 power to rule out Kappa coefficients smaller than 0.61 if the true test-retest agreement is greater than 70%.

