For sensitivity, specificity, PPV, NPV, and concordance we will calculate 95% confidence intervals based upon the binomial distribution. Sensitivity and specificity indicate the effectiveness of a test (here the NHIS survey result) with respect to a trusted “outside” referent, while PPV and NPV indicate the effectiveness of a test (the NHIS survey result) for categorizing people as having or not having a target condition/screening [37].

We will also calculate the report-to-records ratio, the ratio of participants reporting a test (true positives plus false positives) divided by the percentage of tests in the record (true positives plus false negatives). The report-to-records ratio is a measure of net bias in test reporting, where values >1.0 denote overreporting and values <1.0 denote underreporting [38]. All measures will be calculated for each cancer screening test type, as well as by mode of survey administration. For reports to records ratio, 95% confidence intervals will be generated using bootstrap resampling [39].

In our analysis, we will compare our accuracy measures for those completing the survey by web vs. phone. Because survey modality (phone vs. web) was randomly allocated, and we allow participants to change their mode of completion when we contact them, we will perform both an intent-to-treat analysis as well as a separate analysis by modality used.

For responses to the question ‘when did you have your most recent test to check for [cervical/breast/colorectal/lung] cancer’, we hypothesize response accuracy will vary based on the length of time since the last screening exam. We will present the proportion of patients who answer ‘yes’ to having had screening stratified by ranges of time between the survey date and time of last screening exam, including a stratum for those who have not had this exam within the study reporting period of 5 years. In addition, we will present the proportion of patients who had screening exams, within these ranges of time, among those who answer ’yes’ or ’no’ to each question. All analyses will be stratified by cancer site.

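### Plain binomial intervals for PPV, NPV and concordance do not match selection by EMR screening status; with EMR counts fixed, unweighted PPV intervals are about 21% too wide at the planning values and 70–75% at two low-specificity Pap values

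*Protocol article*

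**What the plan says.** **Interval methods** (Primary aims and analyses on validity). One method covers five measures: "For sensitivity, specificity, PPV, NPV, and concordance we will calculate 95% confidence intervals based upon the binomial distribution". For the sixth: "For reports to records ratio, 95% confidence intervals will be generated using bootstrap resampling". The article does not give the resampling unit or say whether resampling is stratified. Table 3 defines all measures from raw cell counts A (true positives), B (false positives), C (false negatives) and D (true negatives).

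**Selection.** Under Stratification and randomization: "Participants are stratified by screening status into three groups based on EMR data". The groups are up to date, screened within five years but overdue, and not screened within five years. The Sample size section adds: "A minimum of 500 gold-standard positive and negative participants for each cancer type are selected". These are minimums, and the design allows fill-in: "If not enough available participants are available to recruit from a given stratum, we select additional participants from other strata".

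**The concern.** In a cross-sectional sample with no selection on EMR status, the number of EMR-positive people (A+C) varies from sample to sample, and PPV = A/(A+B) can be given a binomial interval. Here selection acts on EMR status. Given the EMR-positive and EMR-negative counts, A and B are two independent binomials with different denominators, and A+B is not a simple binomial denominator. The plain formula for PPV or NPV then includes variation in the EMR mix that the design removes, and so does the formula for concordance when sensitivity and specificity differ. An interval labelled 95% covers more than that, and precision obtained by stratifying is lost.

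The excess in the PPV interval is largest where specificity is low, which is where over-reporting is greatest. The Discussion makes the degree of over-reporting one of the things the analyses are to establish.

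**Working it through.** **Inputs.** Planning values of sensitivity (Se) and specificity (Sp) come from the Sample size section: "for sensitivities and specificities >0.80 across all survey modalities". Other Se/Sp pairs come from Table 1: Pap 0.97/0.50 (Canadian survey), 0.96/0.48 (meta-analysis) and 0.972/0.349 (1993 health-plan study); mammography 0.96/0.61 (meta-analysis); colonoscopy 0.95/0.85 and FIT/FOBT 0.58/0.96 (rural study). N+ and N− are the EMR-positive and EMR-negative counts, and N = N+ + N−. An even split with both counts fixed is assumed. The width ratios below depend on the split, not on N.

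**The plan's own figures.** The Wald width is 2 × 1.96 × √(p(1−p)/n).
- p = 0.80: 0.070 at n = 500 and 0.099 at n = 250. Both are below 0.1, so the target is met whether 500 means each status or both together.
- n = 100 ("For subgroups representing 20% (n = 100) of each cancer screening cohort"): 0.118 at 0.9 and 0.157 at 0.8, matching the stated limits of 0.12 and 0.16.

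These calculations are sound for proportions with a fixed denominator.

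**Formulas: plain against fixed-count variance.**
- PPV, logit scale: 1/A + 1/B against 1/A + 1/B − 1/N+ − 1/N−.
- NPV, logit scale: the same with C and D.
- Concordance c: c(1−c)/N against [N+·Se(1−Se) + N−·Sp(1−Sp)]/N².
- Reports-to-records ratio R: for an unstratified bootstrap, {N+[Se(1−R)² + (1−Se)R²] + N−(1−Sp)}/N+², against [N+·Se(1−Se) + N−·Sp(1−Sp)]/N+².

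**Worked case, 0.97/0.50 with 500 + 500.** A = 485, B = 250, PPV = 485/735 = 0.660.
- Plain logit variance: 0.00206 + 0.00400 = 0.00606. Fixed-count: 0.00606 − 0.00400 = 0.00206.
- Multiplying each square root by 0.660 × 0.340 and by 3.92 gives widths of 0.0685 and 0.0400, a ratio of 1.71–1.72.
- Concordance: c = 0.735; √(194.8/139.6) = 1.18.
- Reports-to-records ratio: R = 1.47; √(389.6/139.6) = 1.67.

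**Plain width ÷ fixed-count width, N+ = N−**

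| Se/Sp | PPV | Concordance | Reports-to-records, if bootstrap unstratified |
|---|---|---|---|
| 0.80/0.80 | 1.21 | 1.00 | 1.12 |
| 0.95/0.85 | 1.16 | 1.01 | 1.12 |
| 0.96/0.61 | 1.50 | 1.11 | 1.45 |
| 0.97/0.50 | 1.72 | 1.18 | 1.67 |
| 0.96/0.48 | 1.75 | 1.18 | 1.70 |
| 0.972/0.349 | 2.13 | 1.33 | 2.08 |

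NPV: 1.21 at 0.80/0.80 and about 1.03–1.05 at the other pairs in the table. At 0.58/0.96, with C = 210 and D = 480, it is √(0.00685/0.00285) = 1.55.

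**Checks.** In 40,000 simulated samples with fixed counts, the plain PPV interval covered 98.1% at 0.80/0.80 and 99.9% at 0.96/0.48. An uneven split does not remove the effect: at 0.96/0.48 the PPV ratio is 1.66 for 300/200 and 1.88 for 200/300.

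**If invitations rather than respondents are fixed.** With response rate r, the subtracted terms become r/N+ + r/N−. At 0.96/0.50 with 250 + 250 respondents expected, A = 240, B = 125 and 1/A + 1/B = 0.01217. The PPV ratio is √(0.01217/(0.01217 − 0.008r)): 1.71 at r = 1, 1.22 at r = 0.5 and about 1.12 at r = 0.3. The response rates are assumptions.

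**If PPV is weighted to an assumed population prevalence.** With 500 + 500, plain width ÷ weighted width runs from 0.56 (0.95/0.85, prevalence 0.1: 0.0574 against 0.1016) to 3.8 (0.97/0.50, prevalence 0.8: 0.0685 against 0.0180). The documents give no prevalence.

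**The case against.** The counts are not rigid quotas. They are minimums with fill-in, people are enrolled for several cancers at once, and selected people may not respond; the article itself expects the never-screened to join less often. If the counts vary freely, the PPV excess at 0.96/0.50 falls from 71% to 22% at 50% response and to about 11–12% at 30%. This stands as a limit on size. It does not make the binomial interval right: the EMR mix among respondents is a product of selection and response, and should be conditioned on.

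The planned matrices also cover exam type and indication, which are not the sampling stratifier. That stands too: the figures apply to prior-exam and interval questions.

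Three stronger readings are tempting, and the documents do not support them.
- *The bootstrap is unstratified.* The article says only that it will bootstrap, and a condensed article may leave the details to a full analysis plan. The reports-to-records figures are conditional on an unstratified bootstrap.
- *The error is always about 70%, or at most 70%.* It is 12–21% for PPV and the ratio at 0.80/0.80, and above 100% at 0.972/0.349. Concordance is barely affected when Se and Sp are close.
- *Conclusions about over-reporting or survey mode would fail.* For unweighted estimates the error is conservative. Where it is large, the ratio is far from 1.0: at 0.96/0.50 it is 1.46, with a plain half-width of about 0.11. Subgroup differences are assessed by a Wald-based test, so a loss of power there cannot be derived from these intervals.

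**Conclusion.** The concern holds in limited form. The article states a binomial method for PPV, NPV and concordance, and also states a design that selects on EMR status. For prior-exam and screening-interval questions the two do not match.

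The size rests on three conditions: EMR counts treated as fixed, an even split, and the unweighted Table 3 formulas. Under these, PPV intervals are too wide by about 21% at the planning values, 70–75% at two of the low-specificity Pap values and 113% at the lowest. NPV matters mainly where sensitivity is low (55% at the FIT/FOBT value). Concordance is a small issue, 0–18% at most Table 1 values and 33% at 0.972/0.349.

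With weighting, the direction of the error is no longer certain, and a weighted PPV or NPV has no simple binomial interval. For the reports-to-records ratio the point is a clarification to request, not an error shown. Binomial intervals for sensitivity and specificity remain broadly appropriate, although the three sampling groups are pooled into two. The article's precision figures for them reproduce.

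**What to change.** Amend the interval wording in the primary validity analyses:
- Keep binomial intervals for sensitivity and specificity.
- For PPV, NPV, concordance and the reports-to-records ratio, use a bootstrap that resamples persons within the EMR-status sampling strata, or a stratified delta-method variance.
- Carry any sampling weights through the same calculation, and say whether each reported measure is weighted.
- State explicitly that the ratio's bootstrap is stratified.
- For exam-type and indication matrices, resample within the same sampling strata; do not treat the EMR-positive and EMR-negative margins of those matrices as fixed.

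The cost is a sentence or two of analysis text and a stratum argument in the bootstrap code. No new data or change of design is needed.

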## Methods

### Ethical approval

The recruitment, consent, and study procedures were reviewed and approved by the University of Washington Institutional Review Board (STUDY 12071). KPWA, and MHS sites ceded human subjects review to the University of Washington. Henry Ford Health obtained IRB approval from Henry Ford Health Institutional Review Board (STUDY 16261). To obtain informed consent, study research staff working at each site contact the potential participant by sending an invitation letter with a description of the research project that explains key eligibility requirements and logistical aspects of study participation to their mailing address listed in the site’s EHR. Participants completing the survey over the phone with research staff or via web are explained that their participation on the study is voluntary and their decision to participate will not impact or change the benefits or medical care they receive. Research staff ask the phone-based participants to confirm they have read the study information letter and to provide verbal consent to participate. Participants completing the web version of the survey confirm having read the study information letter and provide digital consent. Verbal and digital consent is documented for each participant in our databases.

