### Recruitment and data collection

Each site is responsible for the recruitment and interviewing of participants from their healthcare system. As described above, each site regularly sends samples of eligible participants to the UW DCC for stratified selection and randomization. The UW DCC returns a list of randomized study participants back to each site. Staff from each site mails recruitment and study information letters to these potential participants. The recruitment letters include information on their assignment to either the phone or web survey. If assigned to the web survey, the recruitment letters include a survey link and QR code along with a unique study ID in two parts (ID and PIN). If assigned to the phone survey, potential participants are notified in the letter that a member of the study team would be calling them to conduct their interviews. Trained interviewers call participants one week after the letters are sent. Participants are called up to 5 times if they do not complete the survey online or are unavailable by phone. For each group, we offer the option to complete the survey via an alternate modality for participants who ask for this option (i.e., phone participants are emailed a web link if they preferred to complete it online and web participants are offered the opportunity to do the survey over the phone).

Invited participants complete eligibility questions and if eligible, respond to the cancer screening questions. The cancer screening survey questions include questions on whether the participant had received cancer screening exams, when they received their most recent cancer screening exam, the type of exam they received, and the main reason for their most recent screening exam. Participants are asked the most important reason for not being screened if the participant has not recently received a cancer screening or is not up to date with the specific type of cancer screening.

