#### Missing data

Missing data due to non-response on both survey waves will be investigated in-depth to look for potential associations with participant demographic factors or with responses to the previous survey. We will use a multiple imputation approach as a sensitivity analysis to examine the extent to which missing data may influence the observed reliability results.

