It is also likely that those who have never been screened may well be less likely to join a study like ours. This would result in an incorrect estimate in screening from surveys that we would not specifically address with these type of validity studies. However, we can estimate response rates by screening status to determine whether or not this is the case in our study.

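### The intent-to-treat phone–web comparison is an as-assigned comparison among respondents, because mode is randomized before an invitation that discloses it, and response by arm is not addressed

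*Protocol article*

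**What the plan says.** **Order of events.** Under Stratification and randomization, samples of eligible people from the sites "are sent to the UW Data Coordinating Center (UW DCC) for stratified randomization for initial survey modality (phone vs. web") and, at three of the four sites, for the timing of the second survey. Under Recruitment and data collection, "The UW DCC returns a list of randomized study participants back to each site", and then "Staff from each site mails recruitment and study information letters to these potential participants". The arm is disclosed at that point: "The recruitment letters include information on their assignment to either the phone or web survey". Consent comes later and takes a different form by mode. Phone participants consent verbally to staff, while "Participants completing the web version of the survey confirm having read the study information letter and provide digital consent" (Ethical approval). Eligibility questions and the screening questions follow.

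**Analysis.** Primary aims and analyses on validity gives random allocation and permitted mode switching as the reason for its two analyses: "we will perform both an intent-to-treat analysis as well as a separate analysis by modality used". All accuracy measures are to be calculated by mode, and no adjustment is mentioned there. The secondary section adds per-protocol and as-surveyed analyses, control for age, sex, race/ethnicity and health system, and a logistic model of correct versus incorrect answers on actual screening status and recency. In both covariate lists the mode term is mode of completion. Subgroup differences are tested by a Wald test at p<0.05 without multiplicity adjustment. A significant mode difference prompts the team to consider adjusting or presenting results separately by mode.

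**Non-response.** Missing data relates non-response to demographics and previous answers, and then says "We will use a multiple imputation approach as a sensitivity analysis to examine the extent to which missing data may influence the observed reliability results". Limitations expects never-screened people to join less often and says "we can estimate response rates by screening status to determine whether or not this is the case in our study". Neither section names the assigned arm.

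**The concern.** An intent-to-treat analysis earns its protection by keeping everyone who was randomized. Here a randomized person who does not respond has EMR data but no self-report, and so no accuracy outcome. The analysed set is therefore formed after randomization, by people who know their arm and are contacted by different routes. Stratified randomization balances the people invited. It does not guarantee balance among those who answer.

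Testing whether mode affects validity is the stated purpose of the embedded trial (Design), and the Conclusions present that trial as a distinctive feature. If respondents in the two arms differ in screening status, recency or recall, a phone–web difference could appear without any mode effect and be read as a randomized result. Because a significant difference can change how the validity results are adjusted or presented, such an artefact could reach the main tables.

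**Working it through.** **1. The plan's own figures.** The article gives no response rates and no figure for the mode contrast. The nearest figure is the interval width below 0.1 for sensitivity or specificity above 0.80 with 500 people (Sample size). Width = 2 × 1.96 × √(p(1−p)/n). At p = 0.80, n = 500 gives 0.070, and 250 per mode gives 0.099. The stated figure reproduces.

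**2. Response depends on EMR status only.** Hold sensitivity (Se) and specificity (Sp) equal in both arms, so there is no mode effect. Let p be the share of respondents who are EMR-positive. From Table 3:

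- Concordance = Se·p + Sp·(1−p)
- PPV = Se·p / [Se·p + (1−Sp)(1−p)]
- NPV = Sp·(1−p) / [Sp·(1−p) + (1−Se)·p]
- Reports to records = [Se·p + (1−Sp)(1−p)] / p

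Se and Sp come from two mammography rows of Table 1: the meta-analysis reporting concordance 0.82, and the study in rural Indiana and Ohio counties. The shares 0.60 and 0.50 are assumptions. They imply an odds ratio of (0.60/0.40)/(0.50/0.50) = 1.5 between the arms.

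| Measure | Se 0.96, Sp 0.61: p = 0.60 | p = 0.50 | Se 0.96, Sp 0.78: p = 0.60 | p = 0.50 |
|---|---|---|---|---|
| Concordance | 0.576+0.244 = 0.820 | 0.480+0.305 = 0.785 | 0.576+0.312 = 0.888 | 0.480+0.390 = 0.870 |
| PPV | 0.576/0.732 = 0.787 | 0.480/0.675 = 0.711 | 0.576/0.664 = 0.867 | 0.480/0.590 = 0.814 |
| NPV | 0.244/0.268 = 0.910 | 0.305/0.325 = 0.938 | 0.312/0.336 = 0.929 | 0.390/0.410 = 0.951 |
| Reports to records | 0.732/0.60 = 1.22 | 0.675/0.50 = 1.35 | 0.664/0.60 = 1.11 | 0.590/0.50 = 1.18 |

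Sensitivity and specificity are the same in both arms by construction. Selection on EMR status alone does not move them.

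**3. Response depends on accuracy itself, for example through recency or recall.** Assume half of those invited answer correctly with probability 0.95 and half with probability 0.75, whatever the mode (0.85 overall). Respondent accuracy in an arm = Σ(response × accuracy)/Σ(response), the two classes being of equal size. Rejection rates come from 20,000 simulated unpooled two-sided Wald tests, with about 500 respondents in total.

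| Response, phone (accurate / less accurate) | Response, web | Phone accuracy | Web accuracy | Spurious difference | Rejection |
|---|---|---|---|---|---|
| 40% / 40% | 40% / 40% | 0.850 | 0.850 | 0 | 4.7% |
| 40% / 40% | 25% / 25% | 0.850 | 0.850 | 0 | 4.9% |
| 40% / 40% | 35% / 25% | 0.850 | 0.520/0.60 = 0.867 | 1.7 points | 8% |
| 40% / 40% | 35% / 15% | 0.850 | 0.445/0.50 = 0.890 | 4.0 points | 27% |
| 30% / 30% | 40% / 20% | 0.850 | 0.530/0.60 = 0.883 | 3.3 points | 20% |

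Row 2 shows that unequal response alone does no harm. Row 5 shows that equal overall response does not rule the bias out. If the two classes are read as more and less recently screened people among the EMR-positive, the same arithmetic applies to sensitivity. The article itself hypothesizes that accuracy varies with time since the last exam.

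**The case against.** The strongest reply is that the secondary section already does much of what is needed. It controls for age, sex, race/ethnicity and health system, and it models correctness given whether and how recently the person was screened, with interactions. These are nearly the variables one would use to weight for response, and a correctly specified outcome model deals with the same measured imbalance. This stands. A reader might infer that the plan does nothing about selective response, and the article does not support that. What remains is that the mode term is mode completed, not assigned, and that the by-mode measures in the primary section are unadjusted.

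Three more points stand. The study is sized on sensitivity and specificity, which do not move under selection on EMR status alone. Calls, and the alternate mode on request, should narrow any response gap. Weighting on EMR and demographic variables repairs selection on recall or engagement only as far as those variables capture it.

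It is also fair to say that the article's use of intent-to-treat is tied to mode switching and that the companion analyses are openly restricted to people surveyed. Detailed weighting could be left to a fuller document. But the label is in the article, and its non-response provisions are directed at reliability and at screening status rather than at the arm.

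A reader might also infer that the mode comparison is biased, or that unequal response rates would prove it. Neither follows. Every response rate and respondent mix used here is assumed, and unequal response alone produced no difference.

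**Conclusion.** The point holds in limited form. The analysis called intent-to-treat compares respondents as assigned. It accounts for mode switching but not for arm-dependent response after the mode is disclosed. Concordance, PPV, NPV and the reports-to-records ratio can then differ by arm with no mode effect. Sensitivity and specificity are safe if selection depends only on EMR status, but not if it depends on recency or recall.

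Under the assumptions shown, a 60% versus 50% EMR mix shifts concordance by 1.8 to 3.5 points. Selection on accuracy gives spurious differences of 1.7 to 4.0 points and Wald rejection of 8% to 27% in place of about 5%. For scale, the standard error of an arm difference with 250 per arm and accuracy 0.87 is √(2 × 0.87 × 0.13/250) = 0.030. The smaller biases are therefore about half a standard error and the largest a little over one. The true size and direction cannot be determined from the documents, and the planned covariate control is a partial mitigation. This is a worthwhile, inexpensive improvement, not a defect that invalidates the trial.

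**What to change.** - Label the analysis *as assigned, among respondents*.
- Report response by assigned arm within EMR screening strata. A crude comparison of response by arm is not enough (last row of the second table).
- Make sensitivity and specificity the main mode contrasts.
- Compare concordance, PPV, NPV and the reports-to-records ratio between arms only after standardizing both arms to one EMR-status and recency mix. In the first example, a common share of 0.55 gives concordance 0.96 × 0.55 + 0.61 × 0.45 = 0.8025 in both arms, and the spurious difference disappears.
- Use assigned mode in the adjusted models of the secondary section for the as-assigned comparison. Keep mode completed for the as-surveyed one.
- Add a sensitivity analysis weighting respondents by the inverse of an arm-specific response probability. Fit it on variables known for everyone randomized: EMR stratum and recency, age, sex, race/ethnicity and site. State that it removes only selection on measured variables.

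The cost is some wording, modest programming with data already drawn for sampling, and slightly wider intervals. No new data collection is needed.
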